### Statistical Analysis

The proportion of patients with recurrent vascular events on days 7 and 90 will be presented as frequency (percentage). Continuous variables will be presented as mean ± SD or median with interquartile range (IQR). Categorical parameters are presented as independent proportions. Baseline information of patients with or without hypoperfusion abnormalities is compared using the Mann-Whitney *U*-test or *t*-test for continuous variables and Fisher's exact test or χ^2^ for categorical variables. Logistic regression analysis will be performed to compare the proportion of recurrence between the two groups. *P* < 0.05 (two-sided) is considered statistically significant. Data analysis will be performed using IBM SPSS (version 20.0) for Windows (SPSS Inc., Chicago, IL, USA). The Data and Safety Monitoring Board will conduct an interim analysis on 45 patients (half of the required sample size). *P* < 0.05 is considered statistically significant in the interim and final analyses.

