### Sample Size and Power Calculation

Two-sided chi-square test is performed at *P* = 0.05 (alpha) to compare the incidence of recurrent vascular events between patients with TIA with PWI-positive and PWI-negative findings. Previous studies have shown that 10% of patients with TIA will relapse; however, the pilot study showed that 34.8% of PWI-positive patients with TIA had recurrent TIA. With the testing power of 80%, the significance level of 0.05 (two-sided), and a 1:1 ratio, with a dropout rate of 5%, a total of 90 patients are needed to detect the difference in relative risks between patients with TIA with PWI negative and PWI positive findings.

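### Interim analysis at 45 patients and final analysis both use P < 0.05, so the overall type I error is about 8–9%, not the stated 5%

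*Protocol article*

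**What the plan says.** The sample-size section of the protocol article plans a two-sided chi-square comparison of recurrence between PWI-positive and PWI-negative patients: "With the testing power of 80%, the significance level of 0.05 (two-sided"), with 1:1 groups and 5% dropout, for a total of 90.

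The Statistical Analysis section then adds a second look: "The Data and Safety Monitoring Board will conduct an interim analysis on 45 patients (half of the required sample size"). The sentence that follows sets the threshold for both looks at P < "0.05 is considered statistically significant in the interim and final analyses".

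The article mentions no alpha spending or adjusted limit. It does not say that the interim is confined to safety, and it names neither the interim endpoint nor a stopping rule.

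**The concern.** A 5% level belongs to a single test. If the same comparison is tested at half the data and again at the end, and significance at either look counts, there are two chances of a false positive. The design level in the sample-size section and the rule in the analysis section therefore cannot both be true.

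The Abstract says the results will confirm whether abnormal Tmax identifies high-risk patients, and the Discussion expects them to guide secondary prevention. Such a claim should carry the error rate stated for it. A claim made at the interim would also rest on very little. With 45 patients split 1:1 there are about 22.5 per group, so even under the planning rates the expected events are about 22.5 × 0.10 = 2.3 against 22.5 × 0.348 = 7.8.

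This is not a detail deferred to an analysis plan. The article states the threshold for both looks, and an analysis plan with adjusted limits would contradict it.

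**Working it through.** **Inputs (protocol article).**
- From Sample Size and Power Calculation: two-sided level 0.05, power 80%, rates 10% and 34.8%, ratio 1:1, dropout 5%, total 90.
- From Statistical Analysis: looks at 45 patients and at the end, each at P < 0.05. The information fraction is 45/90 = 0.5.
- Assumption: the 10% given for TIA patients in general serves as the PWI-negative rate.

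**Step 1. Reproduce the 90.** Pooled-variance formula for two proportions, with p̄ = (0.10 + 0.348)/2 = 0.224:

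n per group = [1.960·√(2·0.224·0.776) + 0.842·√(0.10·0.90 + 0.348·0.652)]² / 0.248² = 43.17

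The total is 86.3, and 86.3/0.95 = 90.9. This agrees with the stated 90 to within rounding. The 90 is therefore a single-look design at 0.05 with no allowance for an interim test.

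**Step 2. Overall error under the stated rule.** Under the null, (Z₁, Z₂) is approximately bivariate normal with correlation √0.5 = 0.707.

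Overall error = 1 − P(|Z₁| < 1.96 and |Z₂| < 1.96) = 0.0831

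If the final analysis has about 86 evaluable patients (information fraction 45/86 = 0.523), the result is 0.0823. Treating the looks as independent would give 1 − 0.95² = 0.0975, which is too high because the looks share data.

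**Step 3. Simulate the uncorrected chi-square test.** Null event rate equal in both groups, 1,000,000 runs per row:

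| Groups (interim, then final) | Null rate | Final look alone | Either look |
|---|---|---|---|
| 23/22, then 45/45 | 10% | 5.9% | 8.7% |
| 23/22, then 45/45 | 20% | 5.4% | 8.8% |
| 23/22, then 45/45 | 30% | 5.3% | 8.8% |
| 18/27, then 36/54 | 10% | 4.9% | 6.8% |
| 18/27, then 36/54 | 20% | 5.0% | 8.1% |
| 18/27, then 36/54 | 30% | 4.9% | 8.0% |

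The interim look adds 8.7 − 5.9 = 2.8 to 8.8 − 5.3 = 3.5 percentage points at 1:1, and about 2 to 3 points at 40:60. The small excess of the 1:1 results over 8.3% comes from the chi-square approximation, not from the second look.

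**Step 4. Limits that restore 5% at information fraction 0.5.**

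| Rule | Interim | Final | Overall error | Power, about 43 evaluable per group |
|---|---|---|---|---|
| Single look | none | P < 0.05 | 5.0% | 79.8% |
| O'Brien-Fleming (2.797, 1.977) | P < 0.005 | P < 0.048 | 5.0% | 79.5% |
| Haybittle-Peto | P < 0.001 | P < 0.05 | 5.02% | 79.9% |
| Pocock (2.178, 2.178) | P < 0.029 | P < 0.029 | 5.0% | 75.4% |

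Repeating Step 1 at the final O'Brien-Fleming level of 0.048 gives 43.71 per group, 87.4 in total.

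**The case against.** **The interim may not test the primary comparison.** The article assigns the look to a Data and Safety Monitoring Board, names no interim endpoint and describes no early stop. The study is also an observational cohort. It is true that the primary comparison is inferred, and the conclusion carries that condition. But the interim shares a significance threshold with the final analysis in a single sentence, and it is timed at half a sample size derived from the recurrence comparison. A safety review needs no P < 0.05 rule. Nor does the inflation depend on stopping, because it arises once significance at either look counts as a finding.

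**The 8–9% depends on the split, the event rate and the test.** This is also true.
- PWI status is observed, not allocated, and the Background and Discussion report hypoperfusion in 25% to 50% of patients. With the chi-square test at a 10% event rate, the overall error is about 6.8% for a 40:60 split and 7.0% for 25:75.
- At a 5% event rate it falls to about 5.7% at 1:1, and below 5% for the unequal splits.
- The Statistical Analysis section names logistic regression for comparing recurrence. An unadjusted Wald test at both looks gives 1.9–3.4% at a 10% rate and 5.0–7.8% at 20–30%.
- Fisher's exact test at both looks gives 3.7–4.1% at 10% and 5.3–6.4% at 20–30%.

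The values below 5% arise because those tests are conservative when events are few, which the plan did not set out to use as protection. In those settings a single look would lie lower still, and the interim look still adds to it. These results qualify the size of the error but do not make the rule correct.

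**Conclusion.** The concern holds, and the rule is wrong as written. Two looks at an unadjusted 0.05 do not have the two-sided 5% level for which the study is sized. The overall error is 8.3% by normal theory, and about 8.7–8.8% for the uncorrected chi-square test at the planned 1:1 ratio with null rates of 10–30%. Roughly 3 percentage points of that come from the interim look.

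This rests on two conditions: that the interim tests the primary recurrence comparison, and that a significant result at either look counts as a finding. The article states the second. The first is the natural reading, and leaving the purpose of the interim unstated is part of the defect. With unequal groups, few events or a conservative test the actual error would be lower, in some cases under 5%, but no provision of the plan secures that.

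**What to change.** Before any interim test is run, replace the last sentence of the Statistical Analysis section with one of the following:

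1. **Keep an efficacy look.** Name the endpoint and the test, and give group-sequential limits for one interim at 50% information. O'Brien-Fleming limits are P < 0.005 at the interim and P < 0.048 at the final analysis. Haybittle-Peto uses P < 0.001 and then about 0.05.
2. **Drop the efficacy look.** State that the 45-patient review covers safety and data quality only, that the primary comparison is not tested, and that 0.05 applies to the final analysis alone.

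The cost is one sentence in the protocol, carried into the analysis plan. Option 2 needs no change in sample size. Under option 1 with O'Brien-Fleming limits the evaluable total moves from 86.3 to 87.4, about one patient. Haybittle-Peto leaves it essentially unchanged. Pocock limits would also hold 5%, but power would fall to about 75%, so they suit this sample size less well.

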## Discussion

Based on a multi-centered community epidemiological study on TIA in Chinese adults, the prevalence of TIA in the Chinese population is as high as 2.4%. The number of patients with TIA in China is as high as 10–12 million (Liu et al., 2007). MRI-based hypoperfusion in patients with TIA is closely related to the time of completing MR imaging. A recent study has shown that hypoperfusion, detected by MRI, is present in 42.4% (25/59) of patients with TIA, and the median (IQR) time of symptom onset to baseline MR-PWI was 5 (4–9) days (Wang et al., 2019a). This is similar to the results of a previous study that has demonstrated the presence of hypoperfusion in 42% (57/137) of patients with TIA, with a median time of 9.2 h from symptom onset to completing MR-PWI (Asdaghi et al., 2013). When the time from symptom onset to the first PWI was shortened, such as a median time of 287 (136–591) min, the presence of hypoperfusion decreased to 25% (16/64) (Lee et al., 2017).

A recent study has shown an incidence of 7.4% of 90-day recurrence of stroke after TIA (Najib et al., 2019). There are multiple potential clinical risk factors for MR perfusion abnormality in the context of TIA. Insufficient local tissue perfusion may be the cause of recurrent TIA (Wang et al., 2019a,b).

This study has its own limitations. First, all the patients were recruited from the same city (Shanghai), and there may be bias in-patient selection. Second, the number of participants is relatively small. Third, treatments for patients with TIA might be slightly different, which will influence the likelihood of TIA recurrence.

The REATTACK trial will provide the power of predicting recurrent vascular events on days 7 and 90 based on hypoperfusion observed on PWI, which is completed within 24 h after symptom onset. This will guide the implementation of effective therapeutics for secondary prevention of TIA and/or stroke.

## Ethics Statement

The studies involving human participants were reviewed and approved by Human Research Ethics Committee of Shanghai Fourth People's Hospital and Tongji Hospital. The patients/participants provided their written informed consent to participate in this study.

## Abbreviations

CIs: confidence intervals
CTA: computed tomography angiography
DWI: diffusion-weighted imaging
FLAIR: fluid-attenuated inversion recovery
IQR: interquartile range
MRA: magnetic resonance angiography
MRI: magnetic resonance imaging
mRS: modified ranking scale
MTT: mean transit time
PWI: perfusion-weighted imaging
TIA: transient ischemic attack
*T*_*max*_: time-to-maximum of residue function
TTP: time to peak.
